### **8.6.1 Adverse Events**

AEs will be classified using a current version of the MedDRA coding dictionary. All reported AEs will be displayed in patient listings. The safety assessment will be based on the incidence of treatment-emergent AEs, including summaries of SAEs, treatment-limiting toxicities, AEs leading to withdrawal, and AEs deemed related to study treatment. The severity of each AE will be assessed using the NCI CTCAE Toxicity Scale, Version 3.0, dated 12 December 2003, Appendix C. If CTCAE does not apply, criteria in described above will be used.

AEs will be categorized and tabulated by system organ class, preferred term, intensity, seriousness, outcome, and relationship to study treatment. Additionally, discontinuations due to AEs, will be summarized. Information collected prior to GC1008 treatment will be presented separately from treatment-emergent signs and symptoms.

If a patient has more than 1 occurrence of an AE for a specific preferred term, the patient will be counted only once for that preferred term. The most intense occurrence of an AE, as well as the most extreme relationship of the AE to the study treatment, will be indicated in cases of multiple occurrences of the same AE.

Changes from pre-treatment in clinical laboratory tests will be summarized. The analysis of laboratory values will also be based on frequencies of abnormal values. Safety outcomes information will be handled by providing counts and percentages if categorical, and by

providing univariate descriptive statistics if continuous. Genzyme will provide cumulative data (as specified in the DMC charter) to the DMC for review.

#### **8.6.2 Laboratory Parameters**

Abnormal clinical laboratory values will be noted as either high or low based on the normal ranges for each laboratory parameter. Changes from pre-treatment in laboratory parameters will be summarized.

#### **8.6.3 Other Safety Assessments**

Listings of vital sign and physical examination data will be presented.

#### **8.7 Maximum Tolerated Dose or Maximum Safe Dose**

The MTD or maximum safe dose will be determined as outlined above. The tolerability of repeat dosing will be evaluated based on the safety profile.

#### **8.8 Pharmacokinetic Endpoints**

Pharmacokinetics of GC1008 will be assessed using noncompartmental methods using actual blood collection times. Areas will be calculated using the linear trapezoidal rule. The elimination rate constant will be estimated based on linear regression of at least 3 data points having a coefficient of determination greater than 0.90. Maximal concentrations and time to maximal concentrations will be determined using observed concentrations. If

noncompartmental methods are inadequate to characterize the pharmacokinetics of GC1008, a compartmental approach under a nonlinear mixed-effects model paradigm will be used.

The following primary endpoints will be calculated: clearance, volume of distribution, and in the case of multiexponential disposition profiles, volume of distribution at steady-state.

The secondary parameters of interest are total area under the curve assuming a single dose from time 0 to infinity, maximal concentration, time to maximal concentration, and half-life.

All PK parameters will be tabulated by individual and summarized by descriptive statistics by cohort. Concentrations will be summarized using descriptive statistics based on nominal collection time. Individual plots will also be generated.

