##### **3.2.2 Secondary Objectives**

- To obtain PK and PD data on GC1008.
  - To evaluate tumor response as a preliminary assessment of clinical activity.
  - To evaluate the relationship between GC1008 exposure, clinical response, and the development of skin lesions
-

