## **6. CLINICAL TRIAL MATERIAL ADMINISTRATION**

### **6.1 Treatments Administered**

GC1008 will be administered as IV infusions. It is suggested that patients be premedicated with diphenhydramine (e.g., 25 to 50 mg orally [PO] or IV) and acetaminophen (e.g., 500 to 650 mg PO) 30 to 90 minutes prior to treatment with GC1008. If diphenhydramine and acetaminophen are ineffective, ibuprofen (e.g., 600 mg PO) may be used.

The first dose of GC1008 will be administered IV in a stepwise manner in which the rate of infusion is incrementally increased. The rate of infusion and drug administration will vary, depending on the patient's weight and the dose administered. Please see the Study Pharmacy Manual for detailed information on administering GC1008.

In Part 1, Dose Escalation, patients will be assigned to receive GC1008 at 0.1 mg/kg, 0.3 mg/kg, 1 mg/kg, 3 mg/kg, 10 mg/kg, or 15 mg/kg (according to the dose-escalation rules). Patients will be observed and have vital signs monitored for 2 hours after completion of GC1008 administration or until discharge, whichever occurs later. The observation period

---

for subsequent infusions may be shortened to 1 hour for patients who did not experience an infusion-related reaction during the first 2 infusions. In all other circumstances, a 2-hour observation period will be required following later infusions.

During Part 1, Dose Escalation, patients will receive their initial dose and then be observed for 28 days for safety. PK and PD samples will be collected during this period. If no DLT occurs, each patient may continue treatment and receive 3 additional treatments, given 14 days apart.

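### Section 8.8 fixes the linear trapezoidal rule for a profile that is mostly exponential decline, so AUC tends to be overstated and clearance understated: a small bias that is cheap to remove

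*Protocol*

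**What the plan says.** Protocol section 8.8 plans noncompartmental analysis using actual collection times and fixes one integration rule: "Areas will be calculated using the linear trapezoidal rule". It continues: "The following primary endpoints will be calculated: clearance, volume of distribution" and, "in the case of multiexponential disposition profiles, volume of distribution at steady-state". Among the secondary parameters is "total area under the curve assuming a single dose from time 0 to infinity". The elimination rate constant comes from "linear regression of at least 3 data points having a coefficient of determination greater than 0.90". A mixed-effects model is the fallback if "noncompartmental methods are inadequate to characterize the pharmacokinetics of GC1008, a compartmental approach" is needed; no criterion for inadequacy is given. Parameters are listed by patient and summarized descriptively by cohort.

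Section 6.1 gives the route: "GC1008 will be administered as IV infusions". Sections 4.1.1 and 4.1.2 have first-dose blood sampling run over 28 days. Section 3.2.2 adds, for Part 2, the objective "To evaluate the relationship between GC1008 exposure, clinical response, and the development of skin lesions".

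**The concern.** After an infusion ends, concentrations fall roughly exponentially, and section 8.8 itself allows for more than one exponential phase. Such a curve is convex, so the chord between two samples lies above it and each declining trapezoid is too large. Clearance is dose divided by AUC, so the error passes to clearance with the opposite sign, and to any volume derived from clearance.

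The error is not the same for every patient. It grows with the ratio of sampling interval to half-life, so faster decline or a missed sample gives a larger error. Differences between patients in AUC and clearance would then partly reflect the integration rule. That matters if AUC is the exposure measure used for the objective in section 3.2.2.

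**Working it through.** The protocol states no PK figure, so there is none to reproduce.

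**Inputs.** From the protocol: linear rule, IV infusion, 28-day first interval, terminal slope from at least 3 points. Assumed, because no half-life is given and Table 7-1 is illegible in the copy at hand: half-lives of 5 to 21 days; a dense schedule (Days 0, 0.04, 0.17, 1, 2, 4, 7, 14, 21, 28) and a thinner one (Days 0, 1, 7, 14, 28); the short infusion treated as instantaneous.

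**One declining interval.** With x = ln 2 × interval / half-life, linear area / true area = x(1 + e^−x) / [2(1 − e^−x)].

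| Interval / half-life | x | Overstatement |
|---|---|---|
| 0.5 | 0.347 | 1.0% |
| 1 | 0.693 | 4.0% |
| 2 | 1.386 | 15.5% |

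**One full profile.** Half-life 7 days, C(0) = 1, k = 0.09902, thinner schedule. Concentrations are 1, 0.9057, 0.5, 0.25, 0.0625.
- Linear areas: 0.9529 + 4.2171 + 2.6250 + 2.1875 = 9.9825.
- Tail: 0.0625 / 0.09902 = 0.6312. Total 10.6137.
- True AUC: 1 / 0.09902 = 10.0989. Ratio 1.051, so AUC is +5.1% and clearance 1/1.051 − 1 = −4.9%.
- Log rule: (1 − 0.0625) / 0.09902 + 0.6312 = 10.0989, no error.
- Day 7 missed: 0.9529 + 7.5121 + 2.1875 + 0.6312 = 11.2837, or +11.7%.

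**Range.** Error in AUC to infinity, with the tail taken from a log-linear fit to the last three samples. The two-phase profile is C = 0.5e^(−at) + 0.5e^(−kt), where a corresponds to a 2-day half-life and k to the terminal half-life shown.

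| Schedule | Profile | 5 d | 7 d | 10 d | 14 d | 21 d |
|---|---|---|---|---|---|---|
| Dense | one phase, linear | +3.2% | +1.9% | +1.0% | +0.5% | +0.2% |
| Dense | two phases, linear | +4.2% | +2.9% | +1.7% | +0.8% | −0.2% |
| Dense | two phases, log-down | +0.5% | +0.5% | +0.4% | +0.1% | −0.5% |
| Thinner | one phase, linear | +8.3% | +5.1% | +2.7% | +1.4% | +0.5% |
| Thinner | two phases, linear | +13.2% | +9.4% | +5.7% | +2.5% | −1.5% |
| Thinner | two phases, log-down | +1.8% | +1.8% | +1.2% | −0.2% | −2.8% |

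The log rule has no error in the one-phase rows. The clearance error for +4.2% is 1/1.042 − 1 = −4.0%, and for +13.2% it is 1/1.132 − 1 = −11.7%.

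**Why one column is negative.** Two phases, 21 days, thinner schedule: true AUC is 10.579 to Day 28 plus 6.012 beyond, 16.591 in all. The linear rule gives 11.035 to Day 28 (+0.456). The fitted slope, still steepened by the early phase at Day 7, is 0.0374 against a true 0.0330, so the tail is 5.302 (−0.710). Net error: −0.254 / 16.591 = −1.5%.

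**A second set of assumptions.** With a 1.5-hour infusion and half-lives of 7 to 21 days, the linear rule gave −0.1% to +2.1% on two denser schedules. It gave +0.1% to +10.6% when nothing was sampled between the end of infusion and Day 7.

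**The case against.** The linear rule is a standard noncompartmental choice, clearly stated and applied to everyone. With dense sampling the error is a few percent at most, and the document does not show that sampling is thin. The PK summaries are descriptive: escalation in section 6.2.1 turns on DLTs, and the second Part 2 cohort on safety. Nothing says that exposure in section 3.2.2 means AUC. Clearance is one of several primary PK endpoints, and a model-based fallback exists. All of this stands, and it keeps the point minor. The fallback helps only if someone judges the noncompartmental results inadequate, and an integration error of this kind need not prompt that judgement.

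The strongest counter-argument is that the log rule can land further from the truth. It does so with a 2-day early phase and a 21-day terminal half-life: −0.5% against −0.2% on the dense schedule, −2.8% against −1.5% on the thinner one, and −8.4% against −4.8% with samples only at Days 0, 1, 14 and 28. The linear rule does better there only because its upward error happens to cancel part of a tail error.

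A reader might infer that AUC is overstated in every patient and always in one direction. The overstatement holds for each declining segment, but not for AUC to infinity under the protocol's own fitted tail, as these cases show. A reader might also fault the lack of a limit on the extrapolated share of AUC. That is commonly left to the SAP, which is not at hand, so it is no finding.

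**Conclusion.** The point holds as a minor one. The rule fixed in section 8.8 overstates declining segments, so it tends to inflate AUC and lower clearance, unequally between patients. Its net size cannot be settled from the protocol. Under the assumed half-lives of 5 to 21 days it is roughly 0–4% of AUC with dense sampling, and about 0.5–13% in size, mostly upward, with samples at Days 0, 1, 7, 14 and 28. It becomes material only where sampling intervals approach a half-life of the phase being sampled. With a slow terminal phase the net error can vanish or change sign. Safety conclusions and dose decisions are not affected.

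**What to change.** Replace the sentence in section 8.8 with: *All areas will be obtained by the linear-up/log-down trapezoidal rule.* That means linear between rising or equal concentrations and logarithmic between falling ones. Recompute any Part 1 values already produced, so that both parts use one method.

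The cost is one sentence, a change of calculation rule in the PK analysis, and a small amount of re-analysis; no new data are needed. The change removes the integration error for a single-exponential decline. It does not remove error from an under-sampled early phase or from the extrapolated tail, so it should not be presented as making clearance unbiased.

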### **8.9 Anti-GC1008 Antibody Analysis**

Serum samples will be collected at the time points specified in Table 7-1 and Table 7-3 and analyzed for the presence of antibodies directed against GC1008. Analyses will be performed using an ELISA-based assay. The presence and relative titer of such human anti-human antibody responses will be assessed and summarized for the patient population.

A total of 4 blood samples in Part 1 and 3 blood samples in Part 2 will be collected over a period of approximately 140 days, with a total blood volume of approximately 12 to 18 mL. One sample will be collected in each course of Extended Treatment (approximately 4.5 mL). Additional samples for anti-GC1008 antibody tests may be requested during long-term follow up, if needed to complete the analyses.

### **8.10 Statistical Analysis Plan**

A statistical analysis plan will be prepared prior to database lock.

### **8.11 Power and Sample Size**

The objective of this study is to assess the safety and PK profile of GC1008. In Part 1, Dose Escalation, the sample size of at least 3 patients in each cohort is the size typically used in a dose-escalation study. Cohorts may be expanded if there is a need to gather additional information on safety. Up to 36 patients will be enrolled in Part 1, Dose Escalation. In Part 2, Patient Expansion, approximately 12 patients will be enrolled, with 2 cohorts of 6 patients each to be enrolled sequentially. The dose level in the second cohort will be determined based on the outcome of the safety review conducted on the initial cohort of 6 patients.

Because patients with 2 types of malignancies will be eligible for this study, the number of patients with a specific type of cancer is small, and meaningful statistics are unlikely. Nevertheless, patients with measurable disease will be assessed by standard criteria, and the objective tumor response rates will be examined. Estimates of response rates will be provided with 90% CIs. For a sample size of 24 and assuming a response rate of approximately 20%, we would expect to observe 4, 5, or 6 responses. Assuming 4 responders, the lower limit of the CI is 5.9%. Assuming 5 responders, the lower limit of the CI is 8.6%. Assuming 6 responders, the lower limit of the CI is 11.5%.

## **8.12 Other Statistical Issues**

### **8.12.1 Significance Levels**

CIIs for tumor response will be based on an alpha of 0.10. All other analyses will use an alpha of 0.05.

### **8.12.2 Missing or Invalid Data**

Missing or invalid data will not be replaced.

### **8.12.3 Computing Environment**

All analyses will be performed using SAS® and WinNonlin (Pharsight Corporation).

